## Abstract

**Background:**

There are increasing studies showing that the use of a lung-protective ventilation strategy has a lung protection effect in patients undergoing abdominal surgery; however, the appropriate positive end-expiratory pressure (PEEP) has not yet defined. Adopting a suitable PEEP may prevent postoperative pulmonary complications. Robot-assisted laparoscopic surgery is the newest and most minimally invasive treatment for bladder cancer or prostate cancer. It is also necessary to consider the effects of Trendelenburg position with pneumoperitoneum on airway pressure and pulmonary function. The role of PEEP during the intraoperative period in preventing postoperative pulmonary complications for robot-assisted laparoscopic surgery is not clearly defined.

**Methods/design:**

A total of 208 patients undergoing robot-assisted laparoscopic radical resection for bladder cancer or prostate cancer will be enrolled and then randomly assigned to a standard PEEP (6–8 cm H_2_O) group and a low PEEP (≤2 cm H_2_O) group. Both groups will receive an inspired oxygen fraction of 0.50 and a tidal volume of 8 mL/kg ideal body weight. Standard perioperative fluid management standardization and analgesic treatments will be applied in both groups. The primary endpoint is postoperative pulmonary complications within 7 days after surgery. Secondary endpoints are the modified clinical pulmonary infection score, postoperative extrapulmonary complications, postoperative surgical complications, intensive care unit length of stay, hospital length of stay, and 30-day mortality.

**Discussion:**

This trial aimed to assess the effects of low tidal volumes combined with intraoperative PEEP ventilation strategy on postoperative pulmonary complications in patients undergoing robot-assisted laparoscopic radical resection for bladder cancer or prostate cancer.

**Trial registration:**

ID: ChiCTR1800019867. Registered on December 2, 2018.

**Electronic supplementary material:**

The online version of this article (10.1186/s13063-019-3363-y) contains supplementary material, which is available to authorized users.

## Background

Robot-assisted laparoscopic surgeries, including robot-assisted laparoscopic radical prostatectomy (RALP) and robot-assisted laparoscopic radical cystectomy (RARC), are the newest and most minimally invasive treatments for bladder cancer or prostate cancer [1, 2]. The incidence of postoperative pulmonary complications (PPCs) in patients undergoing general surgery is about 5%, and 12% to 58% of patients undergoing abdominal surgery will develop a PPC [3, 4]. Furthermore, PPCs are strongly associated with prolonged postoperative hospital stays and a higher risk of mortality [5–7].

Nearly 30% of surgery patients undergoing general anesthesia and mechanical ventilation are at intermediate to high risk for PPCs, according to large cohort studies [4, 8]. Both alveolar overstretching and atelectasis induce the release of inflammatory mediators, leading to lung and systemic organ damage [9]. Lung-protective ventilation, including the use of low tidal volumes and positive end-expiratory pressure (PEEP), aims to prevent atelectasis and improve gas exchange [10, 11]. Furthermore, PEEP has been found to reduce mortality in patients with acute respiratory distress syndrome [12].

Adopting an appropriate PEEP may prevent PPCs. When high PEEP is applied, alveolar may be overinflated and pulmonary vascular resistance is likely to increase; however, use of low PEEP may not prevent atelectasis [9]. A number of studies have shown that, compared with non-protective mechanical ventilation without PEEP, the use of a lung-protective ventilation strategy has a lung-protective effect in patients with healthy lungs who are undergoing abdominal surgery, reducing the incidence of PPC [13, 14]. Although all of these studies recommend the use of a low tidal volume [9, 13–17], the appropriate PEEP has not yet been defined. A multicenter observational study showed that about 20% of patients did not receive PEEP during routine anesthetic practice [16]. In the Intraoperative Protective Ventilation (IMPROVE) trial, a lung-protective ventilation strategy with lower tidal volumes and a PEEP of 6 cm H_2_O was associated with improved clinical outcomes in patients undergoing major abdominal surgery [13]. Furthermore, a protective ventilation strategy with a PEEP of 10 cm H_2_O improved respiratory function and reduced the modified clinical pulmonary infection score (mCPIS) in another study including patients undergoing abdominal non-laparoscopic surgery [14]. However, another study showed that a low tidal volume combined with a low PEEP (3 cm H_2_O) ventilation may increase the risk of PPCs during major surgery such as hepatectomy [17]. In the PROVHILO trial, a ventilation strategy of high PEEP (12 cm H_2_O) did not reduce the incidence of PPCs but more likely caused hemodynamic instability in patients undergoing open abdominal surgery [15]. Therefore, the authors suggested a ventilation strategy of a low tidal volume combined with a low PEEP (≤2 cm H_2_O).

It should be noted that these studies included only open surgeries or various types of abdominal surgery; they did not include patients planning to undergo robot-assisted laparoscopic surgery. Furthermore, it is necessary to consider the effects of steep Trendelenburg (sT) positioning and pneumoperitoneum (PnP) on airway pressure and pulmonary function [18], which can increase intra-abdominal pressure and enhance the cranial displacement of the diaphragm. This displacement will decrease lung compliance and lung volumes and increase lung resistance. Adopting a PEEP of 7 cm H_2_O during RALP, which could improve arterial oxygenation without causing excessive peak airway pressure, has been recommended [19]. Also, a lung-protective ventilation strategy with a lower tidal volume (V_t_) of 6 mL/kg and a PEEP of 8 cm H_2_O was associated with less impaired postoperative pulmonary functions in patients undergoing RALP in another recent study [20].

The role of PEEP during the intraoperative period in preventing PPCs for robot-assisted laparoscopic surgery has not been clearly defined. This study may further improve our knowledge regarding the effects of intraoperative PEEP on PPCs, survival rates, and in-hospital stays in patients undergoing robot-assisted laparoscopic radical resection for bladder cancer or prostate cancer.

## Methods/design

### Objectives of the study

This trial aimed to compare the effects of low tidal volumes combined with standard PEEP (6–8 cm H_2_O) with those of low PEEP (≤2 cm H_2_O) in patients at risk for complications undergoing robot-assisted laparoscopic radical resection for bladder cancer or prostate cancer during general anesthesia in terms of (1) PPCs; (2) mCPIS, postoperative extrapulmonary complications, changes in chest x-ray findings, and oxygenation; (3) intraoperative complications, including hypoxemia, hypotension, and massive transfusion; and (4) postoperative surgical complications, intensive care unit (ICU) lengths of stay, hospital lengths of stay, and 30-day mortality.

### Study design

This unfunded, parallel-group, double-blinded, prospective, randomized controlled clinical trial was registered at http://www.chictr.org.cn (ChiCTR1800019867) and was conducted at the Department of Anesthesiology and Intensive Care of Zhejiang Provincial People’s Hospital. The first patient will be randomly assigned in January 2019. This trial protocol is conducted in accordance with the Consolidated Standards of Reporting Trials (CONSORT) guidelines (Fig. 1). The SPIRIT (Standard Protocol Items: Recommendation for Interventional Trials) 2013 Checklist is presented in Additional file 1.

**Fig. 1 Fig1:**
[figure not shown]
Standard protocol items

### Blinding, data collection, randomization, and record-keeping

#### Selection of the participants

Researchers will be trained prior to investigation. Study data, including patient clinical characteristics, intraoperative respiratory parameters, postoperative outcomes, and laboratory tests, will be recorded in case report forms (CRFs) (Additional file 2).

An independent researcher will randomly assign the participants to the study group (standard PEEP group) and control group (low PEEP group) in a ratio of 1:1. The random sequence will be computer-generated, and participants will be allocated in numerical order with sealed opaque envelopes. The attending anesthesiologist performs anesthesia strictly in accordance with the research protocol and is also responsible for data during the preoperative, intraoperative, and post-anesthesia care unit (PACU) period. The chief surgeon performs the postoperative laboratory testing. An independent researcher will be involved in postoperative follow-up and data collection. Statistical analysis will be performed by a statistician who does not participate in the data collection. Patients, research staff, surgeons, ICU physicians, and the statistician will be unaware of the group allocation. Some preoperative characteristics and laboratory results will be automatically derived from a computer database.

The original data (CRF and relevant records) will be maintained for 10 years and then destroyed in accordance with hospital standards.

#### Selection of the participants

Patients scheduled for elective robot-assisted laparoscopic radical resection for bladder cancer or prostate cancer under general anesthesia will be screened and recruited during preoperative assessment. Patients meeting inclusion criteria will be required to provide written informed consent. The participant can withdraw from the trial at any time.

Inclusion criteria are patients older than 18 years, American Society of Anesthesiologists (ASA) physical status I–III, and body mass index (BMI) between 18 and 35 kg/m^2^. Exclusion criteria are listed as following: emergency surgery or history of lung surgery; history of mechanical ventilation within the 2 weeks before recruitment; non-invasive ventilation or oxygen therapy at home; acute respiratory failure (pneumonia, acute lung injury, or acute respiratory distress syndrome); history of chronic obstructive pulmonary disease, persistent hemodynamic instability, or severe cardiac disease (New York Heart Association class III or IV, persistent ventricular tachyarrhythmias, or acute coronary syndrome); sepsis or septic shock; need for continuous renal replacement therapy; progressive neuromuscular illness; pregnancy; participation in another study; or refusal to participate.

### Time course of the study

#### Preoperative admission

Medical history, ASA physical status, BMI, 12-lead electrocardiogram (ECG), laboratory results, chest x-ray or computed tomography (CT) scan, ARISCAT (Assess Respiratory Risk in Surgical Patients in Catalonia) score (the ARISCAT study; Additional file 3), nutritional risk screening (NRS 2002 tool), and the results of echocardiography and spirometry (in cases of history of coronary artery disease or smoking) will be recorded.

#### Intraoperative care

A central venous catheter and an arterial cannula will be placed before induction of anesthesia. Peripheral oxygen saturation (SpO_2_), arterial blood pressure, heart rate, ECG, end-tidal carbon dioxide tension (EtCO_2_), and bispectral index (BIS) will be monitored continuously. PnP, tidal volume, PEEP, airway pressures including peak pressure and plateau pressure, airway resistance (Raw), dead space fraction (Vds/Vt), core temperature, and arterial blood gas analysis data will be recorded.

Crystalloid (12–15 mL/kg per hour) is infused to maintain hemodynamic stability and a central venous pressure of 5–12 cm H_2_O. Blood loss and vasodilation are supplemented by colloidal fluid.

Routine anesthesia is induced with intravenous dexmedetomidine (1 μg/kg) or midazolam (0.05–0.075 mg/kg), cisatracurium (2 mg/kg), propofol (2–3 mg/kg), and fentanyl (1–3 μ/kg) for tracheal intubation. Anesthesia is maintained with propofol, sevoflurane, and remifentanil infusion to maintain the BIS of 40–50 until skin suturing is completed. Cisatracurium (1.0–1.5 mg/kg) is administered every hour and is adjusted in accordance with the anesthesiologist’s decision.

Ropivacaine is administrated as local anesthetic before and at the end of operation. Fentanyl (1–3 μg/kg) and flurbiprofenaxetil 50 mg are required before remifentanil is stopped.

#### Postoperative care

Patients will be transferred to the PACU after surgery regardless of whether they are still intubated. Postoperative pain management will be suggested to achieve a visual analogue scale (VAS) pain score of less than 3 out of 10 using a patient-controlled intravenous analgesia pump including fentanyl (0.3–0.5 μg/kg), flurbiprofenaxetil (100 mg), and palonosetron hydrochloride (0.25 mg) palazidine.

The ICU physician and surgeon will independently monitor clinical progress and all endpoints by daily physical examinations. Appropriate prophylactic antibiotics and antithrombotic treatments will be administered as required during the postoperative period. Chest x-ray or CT scanning will be performed when clinically indicated. Arterial blood gas analysis will be performed on postoperative day 1 (POD 1) and POD 3, and other laboratory tests will be performed on POD 1, POD 3, POD 5, and POD 7. The examinations will be repeated and microbiology tests will be performed when the development of pulmonary complications is suspected.

#### Study arms and intraoperative ventilation protocol

Patients will be randomly assigned to the low PEEP ventilation group (PEEP ≤ 2 cm H_2_O) or the standard PEEP group (PEEP = 6–8 cm H_2_O) using a volume-controlled ventilation strategy (Datex Ohmeda S/5 Avance; GE Healthcare, Helsinki, Finland) with a tidal volume of 8 mL/kg ideal body weight (IBW), an inspired oxygen fraction (FiO_2_) of 0.50, and an inspiratory-to-expiratory ratio of 1:2. Respiratory rate should be adjusted to maintain EtCO_2_ between 35 and 45 mm Hg, and plateau pressure should be no more than 30 cm H_2_O. IBW is calculated as follows [13]: 45.5 + 0.91 × (centimeters of height − 152.4) for females and 50 + 0.91 × (centimeters of height − 152.4) for males. Recruitment maneuvers (RMs) [21] will be performed immediately after tracheal intubation and every time the ventilator is interrupted until the end of surgery in each group. The compliance of the respiratory system will be calculated as V_t_ / (plateau pressure of the respiratory system − PEEP).

RMs will be performed as follows:Pressure support ventilation (PSV) modePEEP set to 30 cm H_2_OInspiratory gas flow set to the highest valueDuration of the maneuver = 30 s.

A rescue therapy will be applied in case of desaturation (defined as a peripheral SpO_2_ of less than 92%), consisting of increased FiO_2_ to 100% in each group and increasing PEEP in the low PEEP group (Additional file 4).

### Study endpoints

#### Primary outcome measure

The primary endpoint is PPCs, including new atelectasis or infiltrates on a chest x-ray or CT scanning, respiratory failure defined as the need for non-invasive or invasive ventilation or partial pressure of arterial oxygen/fraction of inspired oxygen (PaO_2_/FiO_2_) of less than 300 within 7 days after surgery [21].

#### Secondary outcome measures

Secondary outcome variables are any pulmonary complications and extrapulmonary complications as follows (Additional file 5):Intraoperative complications: pneumothorax confirmed by chest x-ray and any other complications.PPCs within 30 days after surgery. Those PPCs are scored in accordance with a grading scale ranging from 0 to 4 [22] (grade 0 representing no PPCs and grades 1 to 4 representing gradually worse forms of PPCs) within 7 and 30 days after surgery (Table 1).PPCs will also be analyzed separately (Table 1).Pneumonia is defined in accordance with criteria of the Centers for Disease Control and Prevention [23];Purulent sputum;Postoperative hypoxemia and severe hypoxemia [24];Suspected pulmonary infection is described in a previous study [15];Pulmonary infiltrate is defined in accordance with consensus guidelines [25]: chest x-ray demonstrating monolateral or bilateral infiltrate.Atelectasis, pleural effusion, and pneumothorax are identified by chest x-ray.The mCPIS is calculated as previously described [26] (Table 2).Suspected pulmonary complications [14];Requirement for postoperative ventilation (respiratory failure that requires non-invasive or invasive ventilation or both) at any time after surgery in accordance with standard criteria and clinical practice guidelines [22].Postoperative extrapulmonary complications within 30 days after surgery:Criteria for systemic inflammatory response syndrome [12]Sepsis and severe sepsis [12]Septic shock [12]Other extrapulmonary infection including surgical site infection (SSI) [27] and intra-abdominal abscessNeed for postoperative blood transfusionPostoperative surgical complications: anastomotic leakage and need for surgical re-intervention, defined in accordance with consensus criteria [28]Unexpected ICU admission or readmissionICU length of stay and hospital length of stayHospital-free days at follow-up day 30In-hospital mortality and 30-day mortality (all-cause mortality 30 days after randomization).

**Table 1 Tab1:** Grade scale for postoperative pulmonary complications

Grade scale	Detailed description
Grade 1	- Cough, dry - Microatelectasis: abnormal lung findings and temperature greater than 37.5 °C without other documented cause; results of chest radiograph indicates no new findings as compared to pre-operative result - Dyspnea, not due to other documented cause
Grade 2	- Cough, productive, not due to other documented cause - Bronchospasm: new wheezing or pre-existent wheezing resulting in change of therapy - Hypoxemia - Atelectasis: radiological confirmation plus either a temperature of more than 37.5 °C or abnormal lung findings - Hypercarbia, transient, requiring treatment, such as naloxone or increased manual or mechanical ventilation
Grade 3	- Pleural effusion, resulting in thoracentesis - Pneumonia, suspected: radiological evidence without bacteriological confirmation - Pneumonia, proven: radiological evidence and documentation of pathological organism by Gram stain or culture - Pneumothorax - Re-intubation postoperative or intubation, period of ventilator dependence (non-invasive or invasive ventilation) of not more than 48 h
Grade 4	Ventilatory failure: postoperative non-invasive ventilation dependence of at least 48 h or re-intubation with subsequent period of ventilator dependence of at least 48 h

**Table 2 Tab2:** The definition of modified clinical pulmonary infection score

Items	CPIS points		
	0	1	2
Tracheal secretions	Rare	Abundant	Abundant + purulent
Chest x-ray infiltrates	No infiltrate	Diffused	Localized
Temperature, °C	36.5–38.4	38.5–38.9	≤36.5 or ≥39.0
Leukocyte count, per mm^3^	4000–11,000	<4000 or >11,000	<4000 or >11,000 + band forms ≥500
PaO_2_/FiO_2_, mm Hg	>240 or ARDS		≤240 and no evidence of ARDS
Microbiology	Negative		Positive

*Abbreviations*: *ARDS* Acute respiratory distress syndrome, *CPIS* clinical pulmonary infection score, *PaO*_*2*_*/FiO*_*2*_ Partial pressure of arterial oxygen/fraction of inspired oxygen

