### Statistics

Normally distributed variables will be expressed as the mean ± standard deviation and will be compared with the Student’s *t* test. Categorical variables will be compared by using the chi-squared test or Fisher’s exact test. Non-normal continuous variables will be expressed as median (interquartile range) and evaluated with the Mann–Whitney *U* test. Intention-to-treat analyses are performed to compare the composite outcome measure at 7 days in the two groups by the chi-squared test (or Fisher’s exact test as appropriate), and multiple logistic regression analysis adjusting will be performed to identify various risk factors (for the primary outcome and the pulmonary complications at POD 30). Adjusted analyses are performed with the use of robust Poisson generalized-linear-model regression for continuous outcomes and are presented as relative risks with 95% confidence intervals. A *P* value of less than 0.05 will be considered statistically significant, and all reported *P* values will be two-sided. Interim analysis of safety will be conducted after enrollment of the first 200 patients. All analyses will be conducted by using SPSS version 18.0 (SPSS, Chicago, IL, USA) software.

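### PPC has two conflicting definitions: imaging-only atelectasis is a primary event yet scores as no PPC on Table 1, and the secondary imaging and day-30 outcomes do not match the composite

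*Protocol article*

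**What the plan says.** **Primary outcome measure.** A PPC is any of "new atelectasis or infiltrates on a chest x-ray or CT scanning", or "respiratory failure defined as the need for non-invasive or invasive ventilation or partial pressure of arterial oxygen/fraction of inspired oxygen" (the ratio being "of less than 300 within 7 days after surgery"). The imaging component needs no accompanying clinical sign.

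**Secondary outcome measures.** The list includes "PPCs within 30 days after surgery. Those PPCs are scored in accordance with a grading scale ranging from 0 to 4", with "grade 0 representing no PPCs". The grade is taken over both 7 and 30 days. Table 1 puts radiological atelectasis at grade 2 in these terms: "Atelectasis: radiological confirmation plus either a temperature of more than 37.5 °C or abnormal lung findings". For the separately analysed items, the text says "Atelectasis, pleural effusion, and pneumothorax are identified by chest x-ray", and infiltrate is likewise defined on chest x-ray.

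**Postoperative care.** Chest imaging may be x-ray or CT and is done on clinical indication.

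**Statistics.** A multiple logistic regression is planned "for the primary outcome and the pulmonary complications at POD 30". The section does not say how the POD 30 outcome becomes yes or no.

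**The concern.** A secondary severity scale may differ from the primary endpoint. The difficulty is that one term covers both, the secondary text links them by saying that those same PPCs are scored, and the lowest grade is labelled as their absence. If the scale grades the PPCs of the primary endpoint, no primary event should be able to score 0. If it is a separate instrument, the label on grade 0 is wrong.

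What is at stake is which patients count as events in the secondary analyses:

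- the graded outcome at 7 and 30 days;
- the separate analyses of atelectasis and infiltrate;
- the binary POD 30 outcome, which the Statistics section sets beside the primary outcome in the same modelling sentence.

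**Working it through.** The plan gives no figure to reproduce here. The check sets each component of the primary composite against Table 1 and asks what grade a patient with only that finding would receive.

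| Patient's only finding | Primary composite, 7 days | Table 1 | Conflict |
|---|---|---|---|
| New atelectasis on x-ray or CT, temperature not above 37.5 °C, no abnormal lung findings | Event | Not grade 1: microatelectasis needs raised temperature, abnormal lung findings and an unchanged radiograph. Not grade 2: needs raised temperature or abnormal lung findings. Result: grade 0 | Yes |
| New infiltrate | Event | May be grade 3, as suspected pneumonia on radiological evidence | Uncertain |
| PaO2/FiO2 below 300 | Event | Depends on the threshold for grade 2 hypoxemia, which Table 1 does not state | Uncertain |
| Need for ventilation | Event | Mostly grade 3 or 4 | None clear |
| Dry cough | Not an event | Grade 1 | Scale is broader than the composite |

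The first row is the demonstrated contradiction. Because the grade is also scored over 7 days, both classifications apply to the same patient in the same window.

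**Imaging rule.** Suppose atelectasis or an infiltrate is seen on CT only.

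- Primary outcome: counted, since CT is accepted.
- Separate secondary analysis of that item: not counted, since only chest x-ray is named.
- Postoperative care allows CT, so such a case can arise.

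Pleural effusion and pneumothorax are not in the composite. For them, the x-ray rule only means that a CT-detected case is not counted as a secondary event.

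**POD 30 outcome.** The only 30-day scoring that the article gives for PPCs as a whole is Table 1. Against the composite, it is broader (dry cough and dyspnea count) and narrower (atelectasis needs a sign). A logistic model needs a binary outcome, and two readings are open: the composite continued to day 30, or a cut-off on the grade.

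**Illustration of size.** From the sample size section: 188 evaluable patients, so 94 per arm, with 39% and 20% expected to have a PPC.

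- Planned events: 94 × 0.39 + 94 × 0.20 = 36.7 + 18.8 = 55.5, about 55.
- The share that is imaging-only atelectasis is not in the document. Assumed range 10%, 30%, 50%: 0.10 × 55.5 ≈ 6; 0.30 × 55.5 ≈ 17; 0.50 × 55.5 ≈ 28 patients who would be both a primary event and grade 0.

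**The case against.** The strongest reply has four parts.

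- **The scale is a legitimate separate instrument.** A secondary severity scale may be broader than a binary primary endpoint, so a dry cough at grade 1 is no error. The secondary items also include some that were never in the composite, such as purulent sputum and pleural effusion, so they need not add up to it. This stands. It does not rescue the grade 0 label, because the text applies the scale to PPCs under the same name.
- **The conflicting case may be uncommon.** Imaging is done on clinical indication, and many indications would themselves be Table 1 items. This stands as to frequency, and it makes the upper end of the illustration less likely. It does not exclude the case.
- **Details belong elsewhere.** A cut-off for a secondary model is commonly left to an analysis plan, and Additional file 5 is not shown. The missing cut-off alone would therefore be no finding. What remains is that the article's two printed definitions disagree, and a supplement cannot make both true.
- **7-day and 30-day results remain comparable.** A reader might infer that they do not, or that a patient can lose an event between the two dates. The grade is scored at both times, so a like-for-like comparison exists. An event is lost only if the day-7 composite is set against a day-30 grade, and no section plans that comparison.

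**Conclusion.** The point holds in a limited form and is minor. Three things follow from the text:

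- imaging-only atelectasis is a primary PPC and also grade 0;
- the x-ray-only rule drops CT-detected atelectasis and infiltrate from their own analyses;
- the only overall 30-day scoring does not match the composite that the POD 30 model is paired with.

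The primary endpoint, its test and its power are unchanged. The range of about 6 to 28 patients rests on the planning rates and on an assumed 10% to 50% share of imaging-only atelectasis.

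Two stronger readings are not supported. A reader might infer that mild symptoms would dilute the effect and cost power at day 30. That needs a symptom rate that the document does not give and a cut-off at grade 1 that it never states, for an outcome with no claimed power. A reader might also extend the contradiction to every component of the composite. Ventilated patients are mostly captured at grade 3 or 4, and infiltrates and a low PaO2/FiO2 are unresolved rather than shown to conflict.

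**What to change.** Three changes of wording:

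1. **Secondary outcome measures.** Identify atelectasis, infiltrate, pleural effusion and pneumothorax by chest x-ray or CT, as the primary outcome does for the first two.
2. **Statistics.** Define the binary POD 30 outcome as the primary composite followed through day 30.
3. **Grading scale.** Keep the 0–4 grade as it is, as a separate ordinal outcome at 7 and 30 days, and reword grade 0 as *none of the conditions in Table 1*.

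No item needs a new grade. Regrading would depart from the cited scale, and an isolated infiltrate may already fall under grade 3.

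The cost is an edit to two sections, with no added assessments. After day 7, the composite would rest on imaging and blood gases obtained for clinical reasons, since the scheduled blood gases are on POD 1 and POD 3. The edit should be made before outcome data are seen.

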### Data monitoring and handling of implausible values or missing values

A clinical investigator will identify implausible values. Missing continuous variables should be less than 10% and will be replaced by median. Missing values will be replaced by the mean of all plausible data (both groups) of the respective endpoint. Data monitoring is managed by an independent investigator who is not involved in the study. The progress of the study will be evaluated, and the completeness and accuracy of the data (informed consent forms, source data, CRFs, and outcome variables) will be verified.

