### Sample size calculation

The incidence rate of PPCs is 39% in the low PEEP group [15]. The two-tailed chi-squared test is performed, and we estimate that 188 patients are required to provide 90% power to detect a 50% relative difference between the two groups (39% to 20%), and type I error probability was 0.05. Given that the follow-up lost rate is 10%, 208 cases in total are needed. Analysis is computed by using G-Power (version 3.1; Informer Technologies, Inc. Universität Kiel, Germany).

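### Table 1 splits PPC grade 3 from grade 4 by ventilation time alone, so a patient who dies within 48 h of re-intubation is graded better than a survivor ventilated for longer

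*Protocol article*

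**What the plan says.** Under Secondary outcome measures, the protocol article scores PPCs within 7 and within 30 days on a 0 to 4 scale, with "grade 0 representing no PPCs and grades 1 to 4 representing gradually worse forms of PPCs". Table 1 prints the criteria for grades 1 to 4.

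- Grade 3 contains several items. The one for ventilated patients is "Re-intubation postoperative or intubation, period of ventilator dependence (non-invasive or invasive ventilation) of not more than 48 h".
- Grade 4 contains ventilatory failure only: non-invasive ventilation dependence of at least 48 h, or "re-intubation with subsequent period of ventilator dependence of at least 48 h".

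No grade mentions death. In-hospital and 30-day all-cause mortality are separate secondary outcomes. ICU stay, hospital stay and hospital-free days at day 30 are also listed, without definitions. The section refers to Additional file 5, which is not shown.

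**The concern.** For a ventilated patient, the step from grade 3 to grade 4 depends on one quantity: how long dependence on the ventilator lasts. Death cuts that quantity short. A patient dying of respiratory failure soon after re-intubation cannot reach the grade named for ventilatory failure, because the clock stops before 48 h. A survivor who needs longer support does reach it. The scale is meant to run from mild to severe, and at its upper end it reverses the order of these two patients.

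If one PEEP arm had more early deaths on the ventilator, its share of grade 4 patients would be understated. The graded secondary outcome would then look better in that arm than the course of its patients warrants.

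**Working it through.** **Inputs.** The grade criteria come from Table 1. The total of 208 patients (Sample size calculation) and the 1:1 allocation give 104 per arm. The documents give no mortality rate and no figure for this effect, so there is no stated figure to reproduce.

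**Step 1: apply Table 1 as printed.**

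| Patient | Ventilator dependence | Grade |
|---|---|---|
| Re-intubated, dies on the ventilator at 24 h | 24 h | 3 |
| Re-intubated, survives, extubated at 24 h | 24 h | 3 |
| Re-intubated, survives, ventilated 60 h | 60 h | 4 |
| Re-intubated, ventilated exactly 48 h | 48 h | 3 and 4 |

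The death ties with the patient extubated early and ranks better than the survivor ventilated for longer. No other route to grade 4 exists, so no other criterion corrects the first row. The last row follows because not more than 48 h and at least 48 h both include 48 h.

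**Step 2: size on the grade.** Each death within 48 h of re-intubation moves 1/104 = 0.96 percentage points of an arm from grade 4 to grade 3. Assume total mortality of 1% to 3%, which is about 2 to 6 of 208. If 0 to 3 such deaths fell in one arm, the grade 4 share there would be understated by 0 to 3/104 = 2.9 percentage points. The upper end requires all three to die on the ventilator within 48 h.

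**Step 3: the primary endpoint.** Under Primary outcome measure, any need for non-invasive or invasive ventilation within 7 days counts as respiratory failure, whatever its duration. The patient in the first row is a primary event if re-intubated in that window, so the primary comparison is unaffected.

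**Step 4: why hospital-free days need a stated rule.** The article does not define them, and two codings of death fit the text. Assume lognormal stay with median 9 days and log-SD 0.4, and three deaths on postoperative day 3 in one arm against none in the other.

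- Mean stay = 9 × exp(0.4²/2) = 9.75 days, so mean hospital-free days = 30 − 9.75 = 20.25.
- Coded as 30 minus stay, each death scores 27. The arm difference is 3 × (27 − 20.25)/104 = +0.19 days.
- Coded as 0, the arm difference is 3 × (0 − 20.25)/104 = −0.58 days.
- SD of stay = 9.75 × √(exp(0.16) − 1) ≈ 4.1 days. The standard error of the difference is 4.1 × √(2/104) ≈ 0.56 days.

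The sign depends on the coding. The shift in favour of the arm with more deaths is about a third of one standard error. This illustrates the two codings and does not show that the article uses the first.

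**The case against.** **The scale measures pulmonary complications, and death is reported separately.** This holds for one extension of the point. A reader might infer that a patient who dies early with no recorded PPC is wrongly scored 0. Grade 0 means no PPC, so that score is correct on this scale. The defence does not cover the ventilated patient. There the scale misstates pulmonary severity itself, and a separate mortality count does not correct the grade.

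**Early death adds hospital-free days and shortens stay.** A reader might infer this as well. The article only names these outcomes. Scoring deaths as 0 hospital-free days fits the text equally well, and the rules may be in Additional file 5 or an analysis plan, neither of which is shown. A condensed article may leave this out. The missing-value rule ("Missing values will be replaced by the mean of all plausible data (both groups) of the respective endpoint") does not mention deaths and settles nothing here. What remains is a request to confirm the rule.

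**No ordinal test is named for the grade.** This is correct. The Statistics section gives categorical variables a chi-squared or Fisher's exact test, which ignores order. That limits how far the inversion can drive a formal result. It does not remove the problem, because the patient still sits in the wrong cell and the table would still be read as ordered.

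**Few deaths are likely, and a death grade departs from the cited scale.** Both are fair. Patients are elective, ASA I–III, with severe cardiac disease, chronic obstructive pulmonary disease and sepsis excluded. Placing ventilated deaths in grade 4 keeps the 0 to 4 range.

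**Conclusion.** The point holds for Table 1 and is minor. The table is printed in full, so this is a rule as stated and does not depend on unseen material. For ventilated patients it grades by a duration that death truncates. It therefore puts a death within 48 h of re-intubation below a longer-ventilated survivor, on a scale described as progressively worse. The 48 h boundary also overlaps.

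The size is 0.96 percentage points of an arm of 104 per affected death, and zero if there are none. The figures for hospital-free days rest on an assumed number of deaths, an assumed distribution of stay and an assumed formula, so they support no finding against the article. The primary endpoint, the sample size and the mortality outcomes are untouched.

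**What to change.** 1. Add to Table 1 that a patient who dies within the grading window while ventilator-dependent is placed in the worst category whatever the duration. That category can be grade 4, which keeps the cited range, or a separate death category above it, which departs slightly from the cited 0 to 4 scale. Apply the same choice at 7 and 30 days.
2. Make the 48 h boundary exclusive, so that exactly 48 h belongs to one grade only.
3. Confirm in the analysis plan or Additional file 5 that hospital-free days at day 30 are 0 for anyone who dies by day 30, and that in-hospital deaths are not counted as short stays. If the rule is already there, nothing more is needed.

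The cost is a few sentences, with no new data and no change to the sample size. The wording should be fixed before unblinding, because a rule chosen once the deaths are known could be challenged as driven by the results.
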